### Interventions

Patients will be randomly assigned to either the low-intensity training group or the high-intensity training group. Tables 2 and 3 show the training programmes. Patients of both groups will receive, in addition to standard treatment, functional arm training three afternoons per week for three weeks. Each training session will last for 60 min, including a 5-min warm-up. The warm-up will prepare the muscles with ball games. This additional training programme contains five standardised and systematically augmented exercises arranged in a circle. The training includes unilateral, active and functional exercises, which will be practised from a sitting position:lifting objects from the lap to a high desk;pulling a resistance band from vertex high to the lap;pulling a mineral water crate on a desk from the unaffected to the affected side;lifting objects over a wooden block with the elbow placed on the table (like an arm-wrestling position);and pulling a laundry bag which is laying on an exercise mat with a rowing motion.

**Table 2 Tab2:** Overview of the schedule for increasing intensity in the high-intensity arm training group

Session	Exercises	Weight	Repetitions	Increase of weight (if participant establishes 15 repetitions)	Sets	Rest between sets (s)
1	5	80% of 1RM	10–15	By 1 unit of weight	3	120
2	5	As in previous session + increase	10–15	By 1 unit of weight	3	120
3	5	As in previous session + increase	10–15	By 1 unit of weight	3	120
4	5	As in previous session + increase	10–15	By 1 unit of weight	3	120
5	5	As in previous session + increase	10–15	By 1 unit of weight	3	120
6	5	As in previous session + increase	10–15	By 1 unit of weight	3	120
7	5	As in previous session + increase	10–15	By 1 unit of weight	3	120
8	5	As in previous session + increase	10–15	By 1 unit of weight	3	120
9	5	As in previous session + increase	10–15	By 1 unit of weight	3	120

*1RM* one repetition maximum

**Table 3 Tab3:** Overview of the schedule for increasing intensity in the low-intensity arm training group

Session	Exercises	Weight	Repetitions	Increase of repetitions	Sets	Rest between sets (s)
1	5	40% of 1RM	10	n. a.	3	120
2	5	40% of 1RM	11	By 1	3	120
3	5	40% of 1RM	12	By 1	3	120
4	5	40% of 1RM	13	By 1	3	120
5	5	40% of 1RM	14	By 1	3	120
6	5	40% of 1RM	15	By 1	3	120
7	5	40% of 1RM	16	By 1	3	120
8	5	40% of 1RM	17	By 1	3	120
9	5	40% of 1RM	18	By 1	3	120

*1RM* one repetition maximum

The resting time will be 120 s after each exercise and set. During this time, the participant changes position for the next exercise. Therefore, two or three people can train at the same time. The resting time between training sessions should be 24 h. Shorter resting times between training sessions are possible in exceptional cases, e.g. if a training is cancelled. The training will be led by qualified and instructed therapists and intensity will be increased progressively according to Tables 2 and 3. The therapists will have to guide and motivate the participants without an active intervention in the exercise (hands-off), except when danger is imminent.

In the first training, participants will be requested to do the exercise without any weight to find out the maximum ROM. They will attempt to reach this ROM in every repetition or to increase it. Each exercise’s one repetition maximum (1RM) will be tried out for this maximum ROM in as few as possible trials.

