**Fig. 1 Fig1:**
[figure not shown]
*Flow diagram* of study design

The study is conducted at the neurological rehabilitation hospital Asklepioskliniken Schildautal Seesen in Germany. Before the intervention, patients will be randomised in a 1:1 ratio into one of two intervention parallel groups.

The first experimental group will receive, in addition to standard treatment, intensive upper limb strength training with an intensity of 80% of the maximum force (three times per week, over three weeks, 60 min per session, with a total of nine additional sessions). The other group will receive, in addition to standard treatment, functional arm training with an intensity of 40% of the maximum force (with the same quantity, frequency and treatment time as the intervention group). After receiving ethical approval and registration of the study, we started recruiting in our hospital in May 2017. The final assessments will be made in 2018. The study protocol is prepared according to the SPIRIT Statement (http://www.spirit-statement.org/) [27] (see Additional file 1; for the SPIRIT figure, see Fig. 2).

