### Randomisation and concealment of allocation

Each study participant will be randomly assigned to one of two intervention groups, either the low-intensity training group or the high-intensity training group. Allocation will be concealed within an opaque sealed envelope. The computer-generated random allocation sequence list will be carried out using a random-number generator (randomizer.org). Assignments will be enclosed in sequentially numbered, opaque, sealed envelopes and stored at the central study centre. The persons who assess eligibility, obtain informed consent and enrol patients in the trial (SH, CH) have no knowledge of group assignment (Fig. 2). After recruitment and after the initial assessment, the appropriate numbered, opaque, sealed envelope will be opened and the randomisation information will be given to the patient and therapists (but not to the outcome assessors). We will not include further potential covariates in our stratification. However, we will test the influence of different covariates statistically on the main effect of the primary outcome.

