### High-intensity training group

The workload in the arm strength training group will be 80% of 1RM, examined at the beginning of the first training session. Participants will do three sets of ten repetitions of each exercise. Resistance will be increased gradually once the participants are able to perform 15 repetitions according to Table 2.

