### Low-intensity training group

The workload in the low-intensity training group will be 40% of 1RM, examined at the beginning of the first training session. Participants will also do three sets of an increasing number of repetitions of each exercise. In the first training session, they will perform ten repetitions, one more in each following training session, with up to 18 repetitions in the final training session according to Table 3. The resistance will not be changed.

We chose a low-intensity progressive training to compare two true active and potentially effective interventions. One intervention increases by weight and the other by repetitions. This low intensity was often used in therapeutic studies for stroke patients [14, 42].

If the grasp of the objects is not possible, a wrist cuff can be used to fix the grip. The therapists will document ROM, repetitions and intensity for each exercise in each session. If a training is cancelled (because of illness or other liabilities), it will be repeated as soon as possible.

The therapy session will be adjusted, interrupted or terminated if the patient (using continuously monitoring):has pain with a numeric rating scale score > 5;has a body temperature > 37 °C,has > 16 points of Borg’s rating of perceived exertion scale;or has a decline in performance of 30%.

The adherence of the training programme will be documented and reported. All single exercises in the arm training programme are well-known and used routinely under different circumstances for the target patients in our clinic. Our additional training programme with systematically augmented exercises is, however, not described in the medical literature yet. For this reason, we underwent a pilot training programme testing the feasibility of the arm training programme in our clinic with all above-mentioned criteria. In five patients, we found that this pilot training programme might be feasible without any AEs.

Both groups will be supervised by one of two experienced physiotherapists not involved in assessment. To control for co-interventions (standard therapy for the upper limb) during the intervention phase of the study (t0 to t1), we will extract information of the total duration and content of both standard and additional therapy from the daily and weekly documentation of our clinic. Content will be described for each 10-min block.

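### The 1RM that sets the training load in both arms is measured after patient and therapists know the allocation, so the delivered contrast may differ from 80% v 40% by an unknown amount and in an unknown direction

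*Protocol article*

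**What the plan says.** The order of events comes from four places in the protocol article.

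- Study design: "Before the intervention, patients will be randomised in a 1:1 ratio into one of two intervention parallel groups".
- Randomisation and concealment of allocation: "After recruitment and after the initial assessment, the appropriate numbered, opaque, sealed envelope will be opened", and then "the randomisation information will be given to the patient and therapists (but not to the outcome assessors".
- Interventions: in the first training, the patient does each exercise unloaded to find the maximum range of motion, and the "one repetition maximum (1RM) will be tried out for this maximum ROM in as few as possible trials". No other rule for the test is given. Therapists lead the sessions.
- The two arm descriptions: "The workload in the arm strength training group will be 80% of 1RM, examined at the beginning of the first training session" and "The workload in the low-intensity training group will be 40% of 1RM, examined at the beginning of the first training session".

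The arms then progress differently. In the high-intensity arm the weight goes up by one unit once 15 repetitions are reached (Table 2). In the low-intensity arm the repetitions rise from 10 to 18 (Table 3), and "The resistance will not be changed". Neither arm has a planned second 1RM test.

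**The concern.** Training intensity is the experimental variable, and the 1RM converts the assigned percentage into a weight. All the outcome measures listed for baseline are taken before allocation is known. The measurement that sets the dose is not.

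A 1RM search depends on effort and on judgement: how hard the patient tries, and when the tester stops adding load. An instruction to use few trials leaves the stopping point to the tester. A therapist about to load a paretic arm heavily may stop early. A patient who knows that light training follows may try less hard. An error of the same proportion in both arms would leave the 2:1 ratio of loads intact. An error that differs by arm would not, and disclosing the arm before the test makes that possible.

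If it happened, the two programmes would still be compared fairly as delivered, but the delivered programmes would be less certainly the 80% and 40% programmes that the protocol names.

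**Working it through.** **Order of events.** Baseline assessment → envelope opened → arm told to patient and therapists → first training session → unloaded range-of-motion test → 1RM → starting load.

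The tester is not named. Screening process keeps the blinded assessors out of treatment and delivery of the intervention. The low-intensity section says the two supervising physiotherapists take no part in assessment. Interventions has therapists lead the sessions. Together these leave the informed therapists as the only testers that fit the text.

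**The plan's own figure.** Inputs from Sample size: changes of 10 kg and 8 kg, SD 3 kg, alpha 5%, power 80%. The normal approximation gives 2 × (1.960 + 0.842)² × 3² / 2² = 35.3, so 36 per arm. The two-sided t test gives 36.3, so 37 per arm, with power 80.8% at 37. Allowing for 5% dropout, 37 / 0.95 = 38.9, so 39 per arm and 78 in total. The stated figures reproduce, and this point does not dispute them.

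**How a 1RM error enters the load.** Let f be the measured 1RM divided by the true 1RM. Then

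true starting intensity = nominal percentage × f.

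The protocol gives no value of f, so every row after the first is an assumption.

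| f, high arm | f, low arm | High load (% of true 1RM) | Low load (% of true 1RM) | Gap (points) | Ratio |
|---|---|---|---|---|---|
| 1 | 1 | 80 | 40 | 40 | 2.00 |
| 0.90 | 1 | 72 | 40 | 32 | 1.80 |
| 0.75 | 1 | 60 | 40 | 20 | 1.50 |
| 0.75 | 0.75 | 60 | 30 | 30 | 2.00 |
| 1 | 0.90 | 80 | 36 | 44 | 2.22 |
| 1 | 0.75 | 80 | 30 | 50 | 2.67 |
| 0.90 | 1.10 | 72 | 44 | 28 | 1.64 |

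The high-arm figures hold at the first session only, because the weight can rise later. The low-arm weight is the planned weight for all nine sessions.

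**What the table shows.** Both mechanisms described above push f down. Acting in the high arm alone, this narrows the contrast. Acting in the low arm alone, it widens it. Acting equally in both, it keeps the ratio at 2:1 but makes both percentages wrong. The text does not say which applies.

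**Illustration of consequence.** Suppose further that the 2 kg difference scales with the gap in starting load, which the protocol does not say. A gap of 32 points then gives 2 × 32/40 = 1.6 kg and about 62% power at 37 per arm. A gap of 28 points gives 1.4 kg and about 51%. A wider gap would act the other way. These figures show sensitivity only and predict nothing.

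**The case against.** The other side has several good points.

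- **The randomised comparison is sound.** Grip strength is measured by blinded assessors at baseline and after three weeks, and the 1RM is not an outcome. A reader might infer that no result could be tied to the stated intensities. The documents do not support that: the comparison of the two programmes as delivered stays valid, and only the precision of the intensity labels is in question.
- **The high arm partly corrects itself.** A load set too low is raised through the 15-repetition rule. That rule does not correct a load set too high, but it limits how long the narrowing case can last.
- **Fixed resistance in the low arm is intended.** The protocol chose one arm to progress by weight and the other by repetitions. Even a perfect 1RM would leave the low arm below a true 40% as strength grows: a 10% gain in 1RM gives 40 / 1.1 = 36.4%. A reader might take the absence of later adjustment as a fault in itself; it is a feature of the comparator. It matters here only because a first error stays in place.
- **There are partial checks.** Assessment of safety and adverse events links Borg 16 to 80% and Borg 10 to 40% of 1RM and allows the ratings to be used to monitor intensity. Therapists log range of motion, repetitions and intensity at each session, and the same two physiotherapists serve both arms. Gross divergence might be seen. However, no stated rule uses a rating to bring the low arm back to 40%, and an intensity logged as a fraction of 1RM would carry the same error.
- **The test procedure may be fuller elsewhere.** A journal article condenses. That excuses missing detail on how the 1RM is found, but not the order of events, which the article states.

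A reader might also infer that the 60-minute session leaves too little time for a proper search. That depends on an assumed time per repetition and on a rest between 1RM attempts that the protocol does not specify, so it carries no weight here.

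**Conclusion.** The point holds as one of dose fidelity. The protocol takes the measurement that sets the experimental variable after patient and therapists know the arm, although it could be taken just before. An error in the 1RM passes in full into the low-arm resistance for nine sessions and into the high-arm load at the start.

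Size and direction are unknown. With f between 0.75 and 1 in one arm only, the starting gap could lie anywhere from 20 to 50 points around the intended 40. That range is assumed; no figure in the document supports a particular f, or shows that f differs by arm. The conclusion rests on two readings: that the tester is one of the informed therapists, which is inferred, and that a 1RM varies with effort and stopping point.

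There is no internal contradiction, no wrong figure and no threat to the blinded grip-strength comparison. This is a low-cost improvement that removes an avoidable source of differential error.

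**What to change.** Amend Randomisation and concealment of allocation, Interventions, and the two arm descriptions so that:

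1. the training physiotherapists complete the unloaded range-of-motion test and the 1RM search for all five exercises, and record the values, before the envelope is opened;
2. the envelope is opened immediately afterwards, for example at the start of the first session;
3. the starting loads are computed from the recorded values.

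This moves the disclosure and leaves the test where it is. Moving the test to the baseline visit would be less good. It would bring treating staff into an assessment that the protocol reserves for non-treating assessors, and the 1RM could be out of date by the first session in patients who are recovering quickly.

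The percentages, progression rules, blinded assessments and sample size (37 per arm, 78 in total) stay as they are, and no staff or procedure is added. The cost is a few sentences of text and slightly later disclosure: patients and therapists learn the programme only at the first session, so assignment to a programme cannot be arranged beforehand.

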### High-intensity training group

The workload in the arm strength training group will be 80% of 1RM, examined at the beginning of the first training session. Participants will do three sets of ten repetitions of each exercise. Resistance will be increased gradually once the participants are able to perform 15 repetitions according to Table 2.

### Low-intensity training group

The workload in the low-intensity training group will be 40% of 1RM, examined at the beginning of the first training session. Participants will also do three sets of an increasing number of repetitions of each exercise. In the first training session, they will perform ten repetitions, one more in each following training session, with up to 18 repetitions in the final training session according to Table 3. The resistance will not be changed.

We chose a low-intensity progressive training to compare two true active and potentially effective interventions. One intervention increases by weight and the other by repetitions. This low intensity was often used in therapeutic studies for stroke patients [14, 42].

If the grasp of the objects is not possible, a wrist cuff can be used to fix the grip. The therapists will document ROM, repetitions and intensity for each exercise in each session. If a training is cancelled (because of illness or other liabilities), it will be repeated as soon as possible.

The therapy session will be adjusted, interrupted or terminated if the patient (using continuously monitoring):has pain with a numeric rating scale score > 5;has a body temperature > 37 °C,has > 16 points of Borg’s rating of perceived exertion scale;or has a decline in performance of 30%.

The adherence of the training programme will be documented and reported. All single exercises in the arm training programme are well-known and used routinely under different circumstances for the target patients in our clinic. Our additional training programme with systematically augmented exercises is, however, not described in the medical literature yet. For this reason, we underwent a pilot training programme testing the feasibility of the arm training programme in our clinic with all above-mentioned criteria. In five patients, we found that this pilot training programme might be feasible without any AEs.

Both groups will be supervised by one of two experienced physiotherapists not involved in assessment. To control for co-interventions (standard therapy for the upper limb) during the intervention phase of the study (t0 to t1), we will extract information of the total duration and content of both standard and additional therapy from the daily and weekly documentation of our clinic. Content will be described for each 10-min block.

### Criteria for discontinuing or modifying allocated intervention in both groups

Therapy sessions will not occur if any of the following conditions are present:body temperature > 37 °C;repeated pain with a numeric rating scale score > 5 (no pain relief during adjusted training);> 16 points of Borg’s rating of perceived exertion scale in two training sessions;a decline in performance of 30% in two following therapy sessions;rehabilitation team perception that therapy is not appropriate despite absence of the above criteria;refusal of consent;decreased alertness and compliance cannot be handled by the therapist;or if training is not possible for one week, without the chance to catch up.

### Additional information

The standard treatment for the affected arm includes mobilisation, stretching, therapeutic positioning, arm and hand motor training, strengthening exercises, mechanical assisted training, functional training and task-oriented training. The standard treatment will be approximately 30 min of individual physical therapy three times a week and 30 min of occupational therapy three times a week. The duration of therapy will be kept equal in both intervention groups. The total time spent in rehabilitative therapy will be recorded by so-called usual care intervention logs to report the number of physiotherapy and occupational therapy sessions received in the three weeks of the study (as part of the usual care treatment).

For the description of the population and for interpretation of the results, the following data will be documented: age; sex; pedestrian or wheelchair user; time since onset; type of stroke; affected side; number of strokes; Mini-Mental State Examination (MMSE); BI; neglect; pusher syndrome; impaired depth sensitivity; aphasia; apraxia; shoulder-hand syndrome; depression; and information about medication.

### Sample size

Based on the study by da Silva et al., we assume a mean difference of 10 kg in the intervention group and a mean difference of 8 kg in the control group with a standard deviation (SD) of 3 kg [11]. We assume an alpha level of 5% and a statistical power of 80% (beta = 20%) using a two-sample t test for mean differences. We used the G*Power Version 3.1.9.2 power and sample size programme of the university of Kiel, Germany for our sample size calculation (‘G*Power’, 1992–2014). According to the programme, we will need 37 patients per study arm. Because we expect a 5% dropout rate, a total of 78 patients (39 per study arm) would be enrolled to ensure 37 individuals in both intervention arms.

Sample size calculations can be based on clinical meaningful differences, on between-group comparisons of similar studies or conveniently on both.

The study by Lang et al. is the only one which examined the minimal clinical important difference of grip strength; its results are limited by a small sample size and wide standard deviations [33]. There are no further studies which verified these results.

Because of these limitations we decided to use the results of another study which assessed between-group differences in grip strength after upper limb strength training [6].

### Recruitment

Based on our sample size calculation, 78 patients will be recruited from our rehabilitation hospital over a period of nine months. We will screen all patients consecutively from our rehabilitation hospital of the Asklepioskliniken Schildautal in Seesen, Germany and recruited patients who meet our eligibility criteria for our RCT. The research staff will screen lists of patients every second day to recruit continuously and will monitor recruitment. Eligible patients will be screened and receive oral and written information about the study from a researcher later. After signing the informed consent, demographic and clinical characteristics will be measured (baseline assessment, t0). Patients will then be measured three weeks after baseline (t1). Recruitment statistics for every week will be discussed to improve the recruitment procedure. Based on this, the research team discusses updates to recruitment and retention strategies, if necessary. Based on the recruitment rate of a previous study, we find it reasonable to recruit the anticipated sample size for our trial within nine months [18].

